## Abstract

**Background::**

Acupuncture may be a clinically effective treatment for insomnia. We will perform a multicenter, large-scale, single-blinded, randomized controlled trial to compare the differences in the clinical efficacy between the use of singleacupoints and compatibilityacupoints in the treatment of primary insomnia.

**Methods/Design::**

A total of 333 participants will be randomly assigned to 2 acupoint treatment groups or 1 nonacupoint control group in a 1:1:1 ratio by a central stochastic system. The acupuncture groups are: the single acupoint group: Shenmen (HT7); and he compatibility acupoint group: Shenmen (HT7), Baihui (DU20), and Sanyinjiao (SP6). The observation period of this trial will be 10 weeks. All patients will be followed for 1 week before randomization (baseline phase). After randomization, the patients will receive 30 minutes of electro-acupuncture once per day for 5 weeks. In the fourth week after the treatment, follow-up will be performed once. The primary outcome will be the Pittsburgh sleep quality index score at 1 week before randomization and 2 and 8 weeks after randomization. The secondary outcomes will include data from sleep diaries, Athens insomnia scale scores, ShortForm-36 Health Survey scores, electroencephalogram technology results and polysomnogram) results. Patients will be required to complete a sleep diary every day during the treatment period. Patients will also undergo electroencephalogram technology and polysomnogram 1 week before randomization and 5 weeks after randomization. The other secondary outcomes will be measured 1 week before randomization and 5 and 9 weeks after randomization.

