### Operating physician

2.6

The physicians who will participate in this trial will be required to pass training in standard clinical operating procedures.

SOP for the basic operation of acupuncture:

1.DisinfectionDisinfection of the doctor's hands: Before acupuncture, the doctors will wash their hands with soap and water and then wipe their hands with 75% alcohol swabs before holding the needles.Disinfection of the acupuncture site: The local skin at the acupuncture site will be wiped and sterilized with 75% alcohol cotton balls, and a ring will be sterilized from the center to the surroundings.2.NeedlingUsing the 2-handed approach, according to the characteristics of the location of the acupuncture points, which will be used to select the claw cutting or clamping method, the direction and depth of acupuncture will be in strict accordance with the requirements of acupuncture operation.3.Retention of the needlesWe expect that the sham acupuncture points and the needle points will be plugged and twirled, and “deqi”will be performed simultaneously. All needles will be left in place for 30 minutes and will not be removed during the needle retention process.4.Needle removalWith the left thumb and index finger holding the sterile dry cotton ball gently pressed on the acupuncture site, holding the needle in the right hand for slight twisting, the practitioner will slowly bring the needle to the skin, let it rest for a moment, and then take the needle out, pressing the pinhole to prevent bleeding.5.The electroacupuncture operationAfter each acupoint or nonacupoint is needled, auxiliary needles will be used for puncture at locations 2 mm lateral to every acupoint or nonacupoint to a depth of 2 mm without manual stimulation. After needle insertion, transcutaneous electric acupoint stimulation (HAMS: Han's acupoint nerve stimulator, HANS-200, Nanjing, China) will be used for electroacupuncture stimulation at every acupoint or nonacupoint.Each acupuncture needle used for acupoints or nonacupoints and their auxiliary needles will be connected to electricity by the HANS for 30 minutes. The stimulation frequency will be 60/100 Hz, and the stimulation intensity will vary from 0.1 to 1.0 mA until the patients feel comfortable.6.Treatment courseAll patients will receive 25 treatments over a period of 5 weeks, once a day, 5 times consecutively with 2-day breaks every week. Follow-up will be performed in the fourth week after treatment.

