#### Outcome measurement

2.7.1

The primary outcome measure in this trial will be the PSQI, and the secondary outcome measures will include the sleep diary, Athens insomnia scale score, SF-36 score, ET results, and PSG results.

PSQI^[16,17]^ is a self-rated questionnaire that assesses sleep quality and disturbances over a 1-month time period. Nineteen individual items generate 7 “component” scores: subjective sleep quality, sleep latency, sleep duration, habitual sleep efficiency, sleep disturbances, use of sleeping medication, and daytime dysfunction. The sum of scores for these 7 components yields 1 global score. All patients will complete the PSQI 1 week before randomization and in the fifth and eighth weeks after randomization.

The sleep diary^[18]^ will be used to record the patients’ sleep and to collect sleep information to assess the therapeutic effect after treatment. Patients will need to complete the sleep diary every day during the treatment period and complete the CRFs only once a week.

The Athens insomnia scale will be used to record the patients’ self-assessment of sleep disorders. The items include sleep latency, waking up at night, waking up earlier than expected, total sleep time, sleep quality, emotions during the day, physical functioning during the day and daytime sleepiness. Patients will need to complete the Athens insomnia scale 1 week before randomization and at the fifth and the ninth week after randomization.

The SF-36^[19]^ questionnaire consists of 36 items containing 8 subscales each. These subscales consist of 2 higher-level summary scales, namely, the physical (physical function, physical role function, bodily pain, and general health) and psychological (vitality, social function, emotional role function, and mental health) summary scales. Patients will complete the SF-36 1 week before randomization and at the fifth and ninth week after randomization.

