### Sample size

2.8

A power analysis is calculated before conducting this trial, which α = 0.05 and power = 90%. According to the previous pilot study, percentages of responders for the primary endpoint are verum 87.5%, sham 25%. Therefore, the sample size in this trial can be estimated initially according to the following formula. Each group needs at least 111 patients (assuming a 20% dropout rate), 333 patients in 3 groups totally will be enrolled in the study.

$$n=\frac{2{\left(u_{\alpha }^{'}+u_{\beta }\right)}^{2}p(1-p)}{{\left(p_{1}-p_{2}\right)}^{2}}$$

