#### Validity analysis

2.9.1

The efficacy scores for week 0, week 2, and week 4 for patients with primary insomnia will be calculated using the difference between the treatment period and baseline period. These indicators will be described by mean, standard deviation, median, P5, P75, and maximum and minimum values. PP and ITT will be used to analyze the main indicators and overall indicators. Because this study is a multicenter randomized controlled clinical trial, the central effect on the therapeutic effect will be considered in the analysis.

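### The protocol gives three incompatible sets of assessment times for primary efficacy: PSQI at weeks 2 and 8, PSQI at weeks 5 and 8, and efficacy scores at weeks 0, 2 and 4

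*Protocol article*

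**What the plan says.** Four places in the protocol article bear on when primary efficacy is measured.

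- Abstract, Methods/Design: "The primary outcome will be the Pittsburgh sleep quality index score at 1 week before randomization and 2 and 8 weeks after randomization". Of the secondary outcomes other than the sleep diary, EEG technology and polysomnography, the abstract says: "The other secondary outcomes will be measured 1 week before randomization and 5 and 9 weeks after randomization".
- Section 2.7.1 (Outcome measurement) confirms the instrument, "The primary outcome measure in this trial will be the PSQI", and then gives its times: "All patients will complete the PSQI 1 week before randomization and in the fifth and eighth weeks after randomization". It places the Athens scale and SF-36 at weeks 5 and 9, and polysomnography at week 5. It describes the PSQI as a questionnaire that "assesses sleep quality and disturbances over a 1-month time period".
- Section 2.9.1 (Validity analysis): "The efficacy scores for week 0, week 2, and week 4 for patients with primary insomnia will be calculated", as a difference between the treatment and baseline periods. No instrument is named in that sentence, but the section covers the main indicators.
- Section 2.6 (Treatment course) sets 25 sessions over 5 weeks, five a week, and adds: "Follow-up will be performed in the fourth week after treatment". Section 2.1 also has one follow-up, in the fourth week after treatment.

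**The concern.** Both PSQI schedules concern the same instrument in the same role, and they agree on baseline and week 8. They differ on the on-treatment assessment. Under the abstract there is no PSQI at the end of the course; under section 2.7.1 there is none at week 2. Section 2.9.1 does not settle it. It shares week 2 with the abstract, adds a week 4 that is in neither PSQI schedule, and leaves out week 5.

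The two on-treatment times answer different questions. A week 2 value describes early response partway through the course; a week 5 value describes response to the course the trial sets out to evaluate. Under the abstract's schedule the primary outcome would have no end-of-treatment value, while the Athens scale, SF-36 and polysomnography all would.

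The later time has its own mismatch. The PSQI is set for week 8, but the only follow-up falls in week 9, together with the other questionnaires.

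**Working it through.** **The schedules side by side (weeks after randomization)**

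| Source | What is timed | On treatment | After treatment |
|---|---|---|---|
| Abstract | PSQI (primary) | 2 | 8 |
| Section 2.7.1 | PSQI (primary) | 5 | 8 |
| Section 2.9.1 | Efficacy scores | 2, 4 (and 0) | none |
| Abstract and section 2.7.1 | Athens scale, SF-36 | 5 | 9 |
| Sections 2.1 and 2.6 | Follow-up | – | 9 (derived below) |

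No post-baseline week appears in all of the first three rows. Week 2 is in the first and third, week 8 in the first and second, week 5 only in the second and week 4 only in the third.

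**The plan's own figures.** Sessions: 5 per week × 5 weeks = 25, as stated. Observation period: 1 baseline week + 5 treatment weeks + 4 weeks to follow-up = 10 weeks, as stated.

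**Sessions received at each candidate time.** Sessions by the end of week t = 5t, for t up to 5.

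- Week 2: 5 × 2 = 10 of 25 (40%).
- Week 4: 5 × 4 = 20 of 25 (80%).
- Week 5: 5 × 5 = 25 of 25 (100%). This assumes completion at the end of the week; a PSQI completed earlier in week 5 would follow 20 to 24 sessions.

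**Follow-up week.** 5 treatment weeks + 4 = week 9. Week 8 is 8 − 5 = the third week after treatment. Different counting conventions do not explain the gap: the abstract and section 2.7.1 each give week 8 for the PSQI and week 9 for the Athens scale and SF-36 within the same text.

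**What the recall window covers.** Take the PSQI's one month as about 4 weeks (an assumption; a calendar month is slightly longer) and completion at the end of the week.

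- Week 2: 2 − 4 = −2, so half the window lies before randomization.
- Week 5: 5 − 4 = 1, so the window lies wholly within treatment.
- Week 8: 8 − 4 = 4, so the window still includes the last treatment week.
- Week 9: 9 − 4 = 5, so the window is the post-treatment period.

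The differences between weeks 2 and 5, and between weeks 8 and 9, therefore change what the score describes.

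**The case against.** **An article condenses a fuller protocol, and the analysis plan and figures are not shown.** The process chart may carry the correct schedule, and a primary time is commonly named in the analysis plan. This stands to the extent that the lack of a named primary time is no fault of the article by itself. It does not remove the conflict: these are positive statements about the primary outcome that cannot both be complete, and no analysis plan can supply a score that was not collected.

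**Section 2.9.1 names no instrument.** Weeks 2 and 4 could refer to the sleep diary, whose case report form is completed weekly. That is possible, but the section is written for the main indicators, and on that reading the primary outcome has no stated analysis time. Counting weeks 0, 2 and 4 from the end of treatment gives weeks 5, 7 and 9, which still fits neither PSQI schedule, and the sentence refers to the treatment period.

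**Stronger readings that a reader might infer, and that the documents do not support:**

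- *That the primary endpoint itself must be either week 2 or week 5.* Week 8 is in both PSQI schedules and no single time is named. Week 8, or both post-baseline times together, could be primary. The either/or holds only for the on-treatment assessment.
- *That centres will collect different weeks and leave data missing by centre.* Nothing shows that sites work from the abstract. Physicians are trained in standard operating procedures, and the case report form is not visible.
- *That a week 2 endpoint would cost most of the power.* Such a figure needs an assumed fraction of the effect at week 2 and an assumed 90% power at week 5. On the verum–sham rates in section 2.8 (87.5% and 25%), with 111 × 0.8 = 88.8, about 89 evaluable per group, keeping 40% of the 62.5-point difference gives 50% against 25%. Power is then Φ[(0.25 − 1.96 × 0.0726) / 0.0701] = Φ(1.54), about 94% (two-sided 0.05, unadjusted). No effect size is given for single against compatibility acupoints, so no power figure can be derived there.

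**Conclusion.** The point holds as an internal contradiction. The abstract, section 2.7.1 and section 2.9.1 give three time sets for primary efficacy that cannot all be right. Its documented size is in the schedule: the on-treatment PSQI follows 10 of 25 sessions or the full 25, the end-of-treatment week is missing from the stated analysis times, and the PSQI time after treatment is one week away from the only follow-up.

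This rests on five sessions a week as stated, assessment at the end of the named week, and section 2.9.1 applying to the primary outcome. If that last assumption fails, the conflict between the abstract and section 2.7.1 remains.

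The documents do not show that any schedule has been followed inconsistently, or that a time will be picked after results are seen. They do put two on-treatment definitions in print, so either could later be presented as prespecified. Because this concerns the primary outcome and is cheap to correct, it must be settled before analysis.

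**What to change.** 1. Reconcile the abstract, section 2.7.1 and section 2.9.1, and the follow-up timing in sections 2.1 and 2.6, to one PSQI schedule. It should include an end-of-treatment value, as section 2.7.1 already does, which coincides with the Athens scale, SF-36 and polysomnography assessments.
2. State whether the later PSQI belongs to the week 9 follow-up or to a separate week 8 assessment, and describe that assessment if it exists.
3. Rewrite section 2.9.1 so that change scores are computed at the times when the PSQI is collected, and name the instrument. If weeks 2 and 4 refer to another measure, say which.
4. Name one post-baseline time as primary, in the protocol or the analysis plan, before the data are analysed.

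The cost is a wording correction and a clarification to the six centres. No extra visits are needed if the section 2.7.1 schedule is the one in use. If it is not, an end-of-treatment PSQI could be added to the week 5 assessments already planned.

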**Discussion::**

This trial will be helpful in identifying whether acupuncture at compatibility acupoints is more effective than acupuncture at single acupoints.

**Trial registration::**

Clinical Trials.govNCT02448602, Registered 5May 2015, https://www.clinicaltrials.gov/ct2/show/NCT02448602?term=NCT02448602&rank=1

## Introduction

1

Insomnia is characterized by dissatisfaction with sleep quantity or quality and is associated with difficulty falling asleep and maintaining sleep.^[1]^ Most reports suggest that the prevalence rates of insomnia are 5% to 15%.^[2–5]^ Insomnia is a chronic problemand has been associated with erectile dysfunction,^[6]^ burning mouth syndrome,^[7]^ depression, ^[8]^anxiety,^[9]^ and functional gastrointestinal disorders.^[10]^ There are many ways to treat or relieve insomnia, including the “guided fantasy” technique,^[11]^ operation of a homeostatic sleep switch,^[12]^ and cognitive behavioral treatments.^[13]^ Among the dominant disciplines in traditional Chinese medicine, acupuncture and moxibustion are widely applied and promoted in clinical practice due to their safety and efficacy. Many Chinese and foreign studies have demonstrated that acupuncture has hypnotic effects and is effective in treating insomnia.^[14]^ However, questions related to the selection of acupoints to treat insomnia, as well as whether single acupoints or compatibility acupoints have better therapeutic effects, have affected clinical acupoint treatment, and these questions remain open.

Therefore, we will perform this multicenter, randomized, controlled, large-scale trial, first aiming to investigate whether acupuncture is effective in treating insomnia through a comparison with a non-acupoint control group. Second, we will compare the clinical efficacy of single acupoints with that of compatibility acupoints in the treatment of primary insomnia. The work reported in this article is financed by the National Basic Research Program (973 Program: 2014CB543100) in China and is registered with an identifier (NCT02448602) by Clinical Trials.gov in the United States of America.

## Methods

2

### Design

2.1

This study will be a multicenter, large-sample, randomized, controlled trial conducted in the following 6 hospitals: Affiliated Hospital of Changchun University of Traditional Chinese Medicine; The First Affiliated Hospital of Hunan University of Traditional Chinese Medicine; Hengyang Affiliated Hospital of Traditional Chinese Medicine; People's Affiliated Hospital of Traditional Chinese Medicine; China-Japan Friendship Hospital of Jilin University; and QiLu Hospital of Shandong University. The design of this study is in accordance with the guidelines of the HIS Committee on Clinical Trials in Migraine.^[15]^

This trial will include 3 groups (Fig. 1, Fig. 2 ): 2 acupoint treatment groups (single acupoint and compatibility acupoint groups) and 1 nonacupoint control group. A central stochastic system will be used to distribute the patients among the 3 groups equally.

**Figure 1 F1:**
[figure not shown]
Trial flow chart.

**Figure 2 F2:**
[figure not shown]
Trial process chart.

**Figure 2 (Continued) F3:**
[figure not shown]
Trial process chart.

The total observation period of this trial will be 10 weeks. All patients will be followed for 1 week before randomization (baseline phase). After randomization, the patients will receive 30 minutes of electroacupuncture once per day for 5 weeks. In the fourth week after the treatment, follow-up will be performed 1 time.

The single-blind evaluation method will be used in this trial. Nevertheless, the patients will be informed that they will be in either one of the acupoint treatment groups or the nonacupoint control group, which is the most effective way to avoid bias.

To communicate in a timely manner between each subcenter and to improve the efficiency of the trial, central randomization will be used, as performed by the China Academy of Traditional Chinese Medicine clinical evaluation center. The patients will be registered in the groups by phone or network at any time and any geographic location, such that the test manager can monitor the progress of each subcenter subject in real time.

This trial will be performed according to the principles of the Declaration of Helsinki (Version Edinburgh 2000). The trial protocol has been approved by the local institutional review board and ethics committee. Written informed consent will be requested from all participants before registration. All patients will be given enough time to decide whether they should sign the informed consent form, and they will be given treatment options other than acupuncture if they are not willing to participate.

### Patients

2.2

#### Diagnostic criteria

2.2.1

According to the American Psychiatric Association (APA) Diagnostic and Statistical Manual of Mental Disorders –DSM-5 (2013) diagnostic criteria for insomnia, the diagnosis of insomnia must meet the following conditions:

1.The individual reports ≥1 of the following sleep-related complaints: difficulty initiating sleep, difficulty maintaining sleep, waking up too early, or sleep that is chronically non-restorative or poor in quality.2.The sleep disturbance (or associated daytime fatigue) causes clinically significant distress or impairment in social, occupational or other important areas of functioning.3.The sleep disturbance has occurred at least 3 times per week.4.The complaint has lasted at least three months.5.The disturbance is not due to the direct physiological effects of a substance.

#### Inclusion criteria

2.2.2

1.Meets the diagnostic criteria for insomnia.2.Is between 18 and 60 years’ old.3.Is not participating in other clinical trials.4.Is willing to finish the treatments and has signed the consent form.5.Has a PSQI index >7.6.Has an Athens index ≥6.7.Has depression scale and anxiety scale scores ≤50.

#### Exclusion criteria

2.2.3

Patients with any of the following conditions will be excluded:

1.Respiratory-related sleep disorders or circadian rhythm sleep disorders.2.Insomnia caused by drugs (eg, drug abuse, drug therapy) or sleep disorders caused by excessive consumption of alcohol, coffee or strong tea, or other lifestyle factors.3.Insomnia caused by the direct physiological effects of a substance.4.Severe primary diseases involving the cardiovascular, lung, liver, kidney or hematopoietic systems, or other serious primary diseases.5.Pregnancy or lactation.6.Allergic constitutions or susceptibility to infections or bleeding.7.Poor compliance.8.Psychosis.9.Insomnia caused by excessive anxiety, depression, or other causes.

### Elimination and shedding standards

2.3

1.Cases that meet the exclusion criteria.2.Those who fail to comply with the prescribed treatment or have incomplete data affecting the evaluation of efficacy and safety should be excluded.3.Subjects with poor compliance who quit on their own during the course of treatment.4.Combined use of therapeutic methods that are prohibited under this programme or replacement of treatment methods on their own.5.If serious adverse events or complications occur, and it is not appropriate to continue the treatment; treatment should be discontinued.

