### The treatment of removed cases

2.4

1.When a subject drops out, the chief physician should employ methods such as going to the subject's house, making phone calls, or sending letters to try to contact the subject to ask for the reasons for study dropout, to record the last date of treatment, and to complete the study analysis.2.The chief physician should use alternate treatment measures according to the actual situation of the subjects who are no longer in the study because of adverse reactions or treatment ineffectiveness.3.When a subject is assigned a random number, he/she becomes an object of the experimental observation, regardless of future diagnosis or the integrity of the treatment.4.After completing at least half the treatment course, a subject who drops out will be considered an effective evaluation case; less than half of the patients with adverse reactions will not be evaluated and will be evaluated only for adverse reactions. However, patients who violate the test plan (eg, violation of the combination of drugs, violation of the inclusion criteria, and medication compliance) will not be evaluated for efficacy or adverse reactions.

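### Removal rules in 2.3 and 2.4 that are not confined to the per-protocol set conflict with the promised ITT analysis, and they also drop plan violators from the adverse-reaction evaluation

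*Protocol article*

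**What the plan says.** Four places in the protocol article bear on who is analysed.

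- **2.3, Elimination and shedding standards.** Item 2: "Those who fail to comply with the prescribed treatment or have incomplete data affecting the evaluation of efficacy and safety should be excluded". Items 3 and 4 list, with no stated analysis consequence, "Subjects with poor compliance who quit on their own during the course of treatment" and "Combined use of therapeutic methods that are prohibited under this programme or replacement of treatment methods on their own".
- **2.4, The treatment of removed cases, item 4.** A late dropout is kept: "After completing at least half the treatment course, a subject who drops out will be considered an effective evaluation case". The next clause is garbled: "less than half of the patients with adverse reactions will not be evaluated and will be evaluated only for adverse reactions". Those who violate the test plan (the examples given are drug combinations, inclusion criteria and medication compliance) "will not be evaluated for efficacy or adverse reactions".
- **2.4 item 3.** "When a subject is assigned a random number, he/she becomes an object of the experimental observation", and this holds whatever the later diagnosis or completeness of treatment.
- **2.9.1, Validity analysis.** "PP and ITT will be used to analyze the main indicators and overall indicators".

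No sentence ties the 2.3 or 2.4 rules to one of the two analysis sets.

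**The concern.** Compliance, completeness of data, dropout and use of other treatments are all observed after randomization. A rule that uses them to decide who enters the efficacy comparison replaces the randomized groups with selected ones.

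The selection can plausibly depend on outcome. Section 2.4 item 2 itself names adverse reactions and treatment ineffectiveness as reasons for leaving the study. The arms also differ in what the patient experiences: one point, three points, or a 2 mm nonacupoint puncture, with needle manipulation and the DeQi sensation called for at the true points (2.5.1, 2.5.2). Loss therefore need not balance across arms. The arm that sheds more of its non-responders would look better than it is.

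The safety side is affected separately. Leaving violators out of the adverse-reaction evaluation can remove events in patients who were needled.

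**Working it through.** **Step 1. Apply the rules to particular patients.** The course is 25 sessions (2.6), so half is 12.5 sessions.

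| Patient | 2.4 item 3 and ITT (2.9.1) | 2.3 item 2 | 2.4 item 4 |
|---|---|---|---|
| Stops after 5 of 25 sessions | Counted | Excluded as non-compliant or incomplete | Not evaluated for efficacy (natural reading of the garbled clause) |
| Stops after 15 of 25 sessions | Counted | Excluded as non-compliant or incomplete | Evaluated |
| Completes the course but uses a prohibited drug combination | Counted | Excluded if this is failure to comply | Not evaluated for efficacy or adverse reactions |

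The second row shows that 2.3 and 2.4 also disagree with each other. The third row does not depend on the garbled clause.

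**Step 2. How many patients could be affected.** From 2.8: 111 per group, 20% dropout assumed.

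- 111 × 0.20 = 22.2, about 22 per arm, leaving 111 − 22 = 89.
- Across three arms, 333 × 0.20 = 66.6, about 67.

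Section 2.4 item 4 keeps those who completed at least half the course. If half of the dropouts come after that point (an assumption), about 11 per arm are removed and 100 remain.

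**Step 3. Illustrative bias.** The assumptions are mine, not the document's: true response is 50% in both arms (55.5 responders and 55.5 non-responders of 111), control removals are random, and the test is two-sided at 0.05 in the normal approximation.

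Formulas, with n patients left per arm and p1, p2 the expected rates among them:

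- SE = √[p1(1−p1)/n + p2(1−p2)/n]
- z = (p1 − p2)/SE
- false-positive rate = 1 − Φ(1.96 − z) + Φ(−1.96 − z)

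*Case A: 11 non-responders removed from one acupuncture arm, 11 at random from control (n = 100).*

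- p1 = 55.5/100 = 55.5%; p2 = 50%.
- SE = √(0.555×0.445/100 + 0.25/100) = 0.0705.
- z = 0.055/0.0705 = 0.78.
- False-positive rate = 0.122, about 12% against a nominal 5%.

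*Case B, extreme bound: all 22 removed are non-responders, 22 at random from control (n = 89).*

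- p1 = 55.5/89 = 62.4%; p2 = 50%.
- SE = √(0.624×0.376/89 + 0.25/89) = 0.0738.
- z = 0.1236/0.0738 = 1.67.
- False-positive rate = 0.388, about 40%.

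*Case C: equal selection, 11 non-responders removed from each arm.* Both arms show 55.5/100 = 55.5%. The difference is 0 and the false-positive rate stays at 5%.

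**Step 4. Milder assumptions.** Take true response as 40% in both arms and remove only non-responders, at different rates in the two arms.

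| Non-responders removed, acupuncture vs control | Observed rates | False difference | False-positive rate |
|---|---|---|---|
| 20% vs 10% | 45.5% vs 42.6% | 2.9 points | about 7% |
| 30% vs 10% | 48.8% vs 42.6% | 6.2 points | about 14% |
| 20% vs 20% | 45.5% vs 45.5% | 0 | 5% |

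**The case against.** The best defence is that 2.9.1 names both PP and ITT, and that compliance, half-course and violation rules are ordinary content for a PP set. Section 2.4 item 3 keeps every randomized subject under observation, and 2.7.1 says that all patients are recorded to the end of the trial. ITT on all randomized patients, with PP defined by 2.3 and 2.4, is a coherent reading. That stands as a possible reading, but the text does not state it. Dropping violators from the adverse-reaction evaluation also goes beyond anything a PP efficacy set would do.

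The defence does limit the point. A reader might infer any of the following, and the documents do not support them:

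- **The reported ITT result will in fact be a completers' result.** The text leaves open which set the rules govern, so this cannot be established.
- **Everyone who quits or switches treatment is removed from analysis.** Only 2.3 item 2 says excluded. Items 3 and 4 state no analysis consequence, and item 5 concerns discontinuing treatment.
- **Early dropouts are certainly removed.** That clause is garbled, so removal rests on its natural reading.
- **The false-positive rate becomes 40%.** That needs all 22 expected dropouts removed although 2.4 keeps those past half the course, every one of them a non-responder, and purely random removal in control.
- **It is a defect that neither PP nor ITT is named as decisive.** An analysis plan that is not shown may settle this.

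It is also fair to say that a patient who leaves may have no later PSQI under any label. Redefining the set does not by itself recover those data.

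**Conclusion.** The point holds as a conflict between stated rules. Section 2.3 item 2 and the violator rule in 2.4 item 4 are unqualified and cannot be followed together with 2.4 item 3 and an ITT analysis. An unseen analysis plan could choose between these instructions but could not obey them all. The removal of violators from the adverse-reaction evaluation is part of the same fault and is the hardest part to defend.

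The size of any bias cannot be derived from the document. Under the assumed 50% response in both arms it runs from none, when selection is equal, through about 12% false positives in Case A, to an extreme bound of about 40%. Every non-zero figure rests on removal that differs by arm and depends on response. The document makes such removal plausible but does not show it. Because the rules decide who enters the primary comparison and the remedy is mostly wording, this should be settled before analysis.

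**What to change.** 1. State that the ITT set is all randomized patients in the assigned arm, using all PSQI data obtained whether or not treatment continued.
2. Confine the criteria in 2.3 and in 2.4 item 4, including the half-course rule, to defining the PP set, and make PP supportive. Rewrite the garbled clause so that its meaning is clear.
3. Keep all treated patients, including plan violators, in the safety analysis.
4. When dropouts are contacted under 2.4 item 1, ask for the scheduled PSQI as well. That item now asks for the reasons and the last treatment date and does not plainly require an outcome assessment.
5. Reconcile 2.3, 2.4 and 2.9.1 so that one statement governs who is analysed.

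The cost is protocol and analysis-plan wording plus some added follow-up effort. The ITT effect may be somewhat diluted compared with an analysis of compliant patients.
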